## Abstract

**Background:**

It has been suggested that the study of women who survive life-threatening complications related to pregnancy (maternal near-miss cases) may represent a practical alternative to surveillance of maternal morbidity/mortality since the number of cases is higher and the woman herself is able to provide information on the difficulties she faced and the long-term repercussions of the event. These repercussions, which may include sexual dysfunction, postpartum depression and posttraumatic stress disorder, may persist for prolonged periods of time, affecting women's quality of life and resulting in adverse effects to them and their babies.

**Objective:**

The aims of the present study are to create a nationwide network of scientific cooperation to carry out surveillance and estimate the frequency of maternal near-miss cases, to perform a multicenter investigation into the quality of care for women with severe complications of pregnancy, and to carry out a multidimensional evaluation of these women up to six months.

**Methods/Design:**

This project has two components: a multicenter, cross-sectional study to be implemented in 27 referral obstetric units in different geographical regions of Brazil, and a concurrent cohort study of multidimensional analysis. Over 12 months, investigators will perform prospective surveillance to identify all maternal complications. The population of the cross-sectional component will consist of all women surviving potentially life-threatening conditions (severe maternal complications) or life-threatening conditions (the maternal near miss criteria) and maternal deaths according to the new WHO definition and criteria. Data analysis will be performed in case subgroups according to the moment of occurrence and determining cause. Frequencies of near-miss and other severe maternal morbidity and the association between organ dysfunction and maternal death will be estimated. A proportion of cases identified in the cross-sectional study will comprise the cohort of women for the multidimensional analysis. Various aspects of the lives of women surviving severe maternal complications will be evaluated 3 and 6 months after the event and compared to a group of women who suffered no severe complications in pregnancy. Previously validated questionnaires will be used in the interviews to assess reproductive function, posttraumatic stress, functional capacity, quality of life, sexual function, postpartum depression and infant development.

## Background

Currently, more than half a million maternal deaths occur annually worldwide. Although an extremely rare event in developed countries, maternal mortality is higher in less developed countries. Better social conditions, better medical care in cases of severe complication and family planning are factors that contribute to reducing maternal mortality [1].

Nevertheless, quantifying maternal mortality in Brazil is a complex task. The Ministry of Health estimates the maternal death ratio at 75 maternal deaths per 100,000 liveborn infants [2]. Reflecting the complexity of this estimate, other agencies, using different methods, have calculated maternal death ratios twice or even four times higher than the official figures [3,4].

Notwithstanding, the recorded cases of maternal deaths constitute a tiny proportion of the whole problem. Around the world, millions of women present severe maternal complications every year and the precise size of this specific population currently remains unknown. For this reason, women who have survived severe complications of pregnancy have in recent years sparked the attention of investigators and healthcare administrators. The World Health Organization (WHO) developed the maternal near-miss approach, a tool to uniformly identify near-miss cases and evaluate quality of care provided to women presenting severe complications. WHO defines a maternal near miss case as a woman who nearly died but survived a complication that occurred during pregnancy, childbirth or within 42 days of termination of pregnancy [5].

Therefore, the study of maternal near-miss cases has been suggested as a practical alternative to the surveillance of maternal morbidity and mortality, mainly in view of the larger number of cases and because the woman herself is able to provide information on the event and on the difficulties she had to face. It is believed that auditing near-miss cases would enable even smaller services to evaluate how the determinants of severe maternal morbidity (and consequently the determinants of maternal death) affect their users and services [6,7].

In addition, little is known on the long-term repercussions of severe, life-threatening complications related to pregnancy. An acute stress disorder associated with the occurrence of severe maternal complications has been suggested, but further research is needed. [8]. The repercussions of these events may lead to adverse effects in the women and their children, may negatively affect their quality of life and may persist for extended periods of time after the event [9-12].

Among the possible repercussions, studies have been carried out to evaluate the psychological impact and occurrence of posttraumatic stress disorder (PTSD), postpartum depression and changes in sexual health following delivery [10,13-17]. Considering that other factors such as mode of delivery, medical interventions and obstetrical complications [9,18,19] negatively affect women's quality of life, it is probable that in dramatic situations such as near-misses such repercussions would be even more evident. According to some authors, evaluation of the state of health, quality of life and sexual function of patients who suffered severe complications is poorer in the immediate postpartum period [15,20-23].

Nevertheless, doubts remain with respect to the long-term health status of women who suffer severe acute maternal morbidity and near-miss. Investigation of various aspects related to mental health and quality of life may offer a valuable perspective on the effect of maternal morbidity on the life of these women.

Studying the occurrence of severe complications in pregnancy and the factors associated with this event will result in a greater understanding of the process that occurs in these women taking them from a state of health to one of sickness. Further knowledge on this issue may collaborate towards improving public policies and the healthcare provided to women who develop severe acute maternal morbidity.

Therefore, the objective of the present project is to evaluate this issue using clear goals to differentiate it from previous studies. These goals include estimating the frequency of the occurrence of maternal near-miss using a uniform set of criteria, carrying out a multicenter investigation into the quality of care provided to women with severe complications of pregnancy and performing a longitudinal evaluation of the quality of life of these women following the event.

## Objectives and Hypothesis

The overall objective is to develop a nationwide network of scientific cooperation for the surveillance of severe maternal complications and maternal near-miss and their consequences.

### Specific objectives

• To determine the frequency of maternal near-miss in healthcare facilities of different levels of complexity situated in different regions of Brazil, using the World Health Organization (WHO)'s new set of criteria for near-miss [5];

• To determine the frequency of non-near-miss severe maternal morbidity in these facilities using specifically defined potentially life threatening conditions;

• To evaluate the association between the indicators of organ dysfunction used to define maternal near-miss and the risk of maternal death;

• To determine the frequency of near-miss and non-near-miss severe maternal morbidity according to age-group and specific causes;

• To examine the occurrence of avoidable factors and other factors associated with maternal near-miss;

• To investigate the repercussions of severe maternal morbidity and near-miss on the quality of life of survivors up to six months after the event;

• To investigate the presence of sexual dysfunction, posttraumatic stress disorder and postpartum depression, as well as women's perception of their functional status in routine activities in the six months following an occurrence of severe maternal morbidity.

• To investigate the immediate perinatal outcome and subsequent neuromotor and weight-height development in children born from pregnancies associated with severe maternal morbidity.

### Main hypotheses

In survivors of severe acute maternal morbidity:

• health and quality of life would be poorer;

• posttraumatic stress would be more common;

• postpartum depression would be more common;

• sexual function would have deteriorated and the woman's return to sexual activity would take longer;

• functional status in routine activities would be evaluated as poorer.

In the children born from a pregnancy associated with severe maternal morbidity:

• immediate perinatal outcome would be poorer;

• the occurrence of impaired neuromotor and weight-height development would be significantly higher.

## Methods/Design

This study has two components: a multicenter cross-sectional study and a concurrent cohort study.

The cross-sectional study will be implemented in 27 referral obstetric units in different geographical regions of Brazil, which have already joined the initiative for building a national network for studies on maternal and reproductive health. Over a 12-month period, the principal and local investigators will carry out prospective surveillance and will collect data for the identification of maternal near-miss and non-near-miss cases, severe maternal morbidity (potentially life threatening conditions) and maternal deaths. To determine the number of collaborating centers to be included in the present study, calculation of sample size took into consideration the number of deliveries that would have to be monitored to identify cases of near-miss and maternal deaths. Previous studies have estimated a maternal near miss incidence of approximately 8 cases per 1000 deliveries [24] and a Brazilian maternal mortality ratio of 140 per 100,000 LB. Therefore, a total of approximately 75,000 deliveries would have to be monitored in order to identify around 100 maternal deaths and 600 maternal near miss cases. These numbers are believed to be sufficient to evaluate the use of the new criteria for near-miss established by the World Health Organization in 2009 [5] and to perform analysis allowing for level of complexity of health facility, age group and specific cause.

The study population will consist of all the women admitted to the participating hospitals during the study period in whom organ dysfunction is registered (maternal near-miss, Appendix 1), in whom one of the diagnoses defined as non-near-miss severe maternal morbidity is present (Appendix 2), and those who died or were transferred to another healthcare service because of their bad health condition.

For the multidimensional analysis of the repercussions of severe maternal morbidity, a concurrent cohort, specific population study will be carried out with an externally selected comparison group. The main exposure factor will be the occurrence of severe maternal morbidity (both maternal potentially life threatening or near miss conditions). During the second half of the cross-sectional study, a sample of women identified as having severe maternal morbidity will be selected and invited to participate in the longitudinal evaluation. There will be a comparison group composed of women who did not suffer severe maternal morbidity. These women will be randomly selected externally in a proportion of 1:1 from postpartum women in the rooming-in wards of the same maternity hospitals as the cases. Controls will be selected at random and balanced according to mode of delivery, maternal age and gestational age at the time of delivery.

### Main outcomes

#### Maternal near-miss

A woman who fulfills one of the clinical, laboratory or management criteria representing severity as defined by WHO [5] and who survives a complication occurring during pregnancy, childbirth or within 42 days postpartum.

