#### Maternal death

Death of a woman during pregnancy or within a 42-day period following the end of pregnancy irrespective of the duration or localization of the pregnancy, resulting from any cause related to or aggravated by the pregnancy or by measures taken with respect to it; however, not from accidental or incidental causes.

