### Data Collection and Procedures

#### Cross-sectional component

Research assistants, referred to as local coordinators, will review the charts of hospitalized patients on a daily basis in search of cases with one of the conditions identifying severity (Appendix 2). In cases found with these diagnoses, the relevant hospital records will be reviewed for data collection following the women's hospital discharge, death or transfer to another healthcare facility. Data unavailable on the chart but of interest to the study will be obtained from the attending medical team. For each case included, data will be collected on the demographic and obstetric characteristics of the patient, the primary determinant of maternal near-miss (the first complication to occur in the chain of events leading to severe maternal morbidity), the duration of hospitalization (prior to delivery, following delivery and total time), the occurrence of indicators of maternal near-miss at any time during hospitalization, indicators of perinatal outcome and conditions of the woman at discharge from hospital.

These data will be collected on a previously coded form developed specifically for this purpose. A central database will be constructed and the data will be included by the local investigators themselves using electronic forms. The manually completed forms will be filed and made available at technical visits for the purpose of quality control.

For the electronic inclusion of data, each center will have its own restricted area on the study website where password-protected access will be granted only to cases included at that center. An overview of all the cases included in the network will be provided in the form of monthly graphs and tables containing the number of cases included by each center. In addition, the reported diagnoses will be provided by the coordinating center on the main page of the website.

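### Maternal death is defined to day 42, but status is observed only to discharge, death or transfer, so unlinked later deaths count as survivors in the organ-dysfunction analysis

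*Protocol article*

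**What the plan says.** Under Main outcomes, Maternal death is "Death of a woman during pregnancy or within a 42-day period following the end of pregnancy", from a cause related to the pregnancy. A maternal near-miss is a woman who meets one of the WHO severity criteria and "who survives a complication occurring during pregnancy, childbirth or within 42 days postpartum"; Appendix 1 repeats this.

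Under Data Collection and Procedures, Cross-sectional component, cases are found by daily review of inpatient charts, and then "the relevant hospital records will be reviewed for data collection following the women's hospital discharge, death or transfer to another healthcare facility". The items recorded include "the occurrence of indicators of maternal near-miss at any time during hospitalization" and "conditions of the woman at discharge from hospital".

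Methods/Design sets the population as "all the women admitted to the participating hospitals during the study period in whom organ dysfunction is registered", women with one of the Appendix 2 diagnoses, and "those who died or were transferred to another healthcare service because of their bad health condition". Centres also report monthly totals of deliveries, live births and maternal deaths. Ethical aspects states that chart data are taken without identifying the woman.

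One specific objective is to relate the organ-dysfunction indicators to the risk of maternal death. Data analysis estimates that association with odds ratios.

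**The concern.** Survival is what separates a near-miss from a maternal death. The death outcome runs to day 42, but the woman's status is recorded when she leaves hospital. No vital-status check is described for women discharged or transferred alive, and no way of linking a later admission to the index record.

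The analysis at stake is organ dysfunction against death. Death is its scarce outcome, at about 100 expected events against 600 near-misses. A woman with an Appendix 1 criterion who leaves alive and dies by day 42 is a death by the protocol's definition, yet a survivor in its data. An analysis plan cannot repair this later, because the information would not have been collected.

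Transferred women are the clearest instance. They are in the study population because their condition was bad, and nothing is described for them after transfer.

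**Working it through.** **Planning figures** (Methods/Design: 75,000 deliveries, 8 near-misses per 1000 deliveries, 140 deaths per 100,000 live births).
- Near-misses: 75,000 × 8/1000 = 600, as stated.
- Deaths: 75,000 × 140/100,000 = 105, consistent with the stated figure of around 100. Deliveries stand in for live births here.
- No deduction is made for deaths outside the hospital stay.

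**Definition against observation.**

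| | Definition | Observed in the cross-sectional component |
|---|---|---|
| Death | to day 42 after the end of pregnancy | to discharge, death or transfer |
| Near-miss, the complication | arises up to 42 days postpartum | any stay in a participating hospital |
| Near-miss, survival | no end date given; a death by day 42 makes it a maternal death | status at discharge |

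The first and third rows do not match. The second largely does for hospital-based case finding, because any admission to a participating hospital is eligible.

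**Routes past the index stay.**
- Readmission to a participating hospital is captured. Without linkage, one woman could appear as a near-miss on one record and a death on another.
- Monthly death totals are centre-level counts. They cannot move an individual woman from near-miss to death.
- The 3- and 6-month interviews cover a consenting sample from the second half of surveillance and are not described as a source of vital status.

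**Size, by assumption only.** The documents do not give the share *f* of deaths that occur after discharge or transfer. Taking *f* from 5% to 15%, missed deaths = 105 × *f*. If every such woman met an Appendix 1 criterion, was counted as a near-miss survivor, and none was readmitted and linked, then deaths/(deaths + near-misses) = 105(1 − *f*)/705.

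| *f* | Missed deaths | Deaths observed | Share of deaths |
|---|---|---|---|
| 0 | 0 | 105 | 105/705 = 14.9% |
| 5% | 5.25 | 99.75 | 99.75/705 = 14.1% |
| 10% | 10.5 | 94.5 | 94.5/705 = 13.4% |
| 15% | 15.75 | 89.25 | 89.25/705 = 12.7% |

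For any given *f* these are the largest effects, since every captured readmission reduces them.

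**Direction for the odds ratio.** For one criterion, let *a* and *b* be deaths and survivors with it, and *c* and *d* those without it, so OR = *ad*/(*bc*). If the same share *f* of deaths is missed in both groups and counted as survivors, the observed value is OR × (1 + *fc/d*)/(1 + *fa/b*). When OR > 1, *a/b* exceeds *c/d*, so the observed odds ratio is pulled towards 1. If the missed share differs between groups, the direction is not fixed.

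**The case against.** The strongest reply is that in the near-miss definition the 42 days date the complication, not survival. A woman admitted on day 30 with organ dysfunction is eligible and found. That stands, and so do four related points.
- Admission to any participating hospital counts, not only the delivery stay, and monthly death totals are collected as well.
- The objectives ask for frequencies in health facilities, and rates are calculated by centre. The article does not present them as complete 42-day population figures.
- A maternal mortality ratio is a planning input here, not an objective, so understating it is not the harm.
- The article is condensed, and a manual of operation exists that is not shown.

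A reader might therefore infer too much: that everyone who dies or becomes a near-miss after discharge is counted as a survivor or not at all, or that the near-miss frequency itself fails for want of 42-day follow-up. The documents do not support either, because readmissions to participating hospitals are within scope.

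A reader might also expect the planned 3-month call to bound the misclassification. It cannot. It reaches a consenting second-half sample, a woman who has died cannot answer, and no proxy contact is described.

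The mismatch for death remains. The article does state when status is recorded, and that is discharge rather than day 42. A manual of diagnostic definitions would not by itself supply later vital status.

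**Conclusion.** The point holds for death and for the survival part of near-miss. As described, the cross-sectional component observes death in participating hospitals, while the definition runs to day 42. The women affected are those who met an Appendix 1 criterion, left by discharge or transfer, and died by day 42 without a linked readmission to a participating hospital. They fall on the survivor side of the organ-dysfunction odds ratios.

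The bias cannot be sized from the documents. The range of 5 to 16 deaths out of about 105 rests wholly on an assumed 5% to 15%, before any reduction for readmissions. The surveillance remains sound for facility-based frequencies. What needs to change is how the death and survival outcomes are defined and what the death contrast is said to show.

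**What to change.** - Define the cross-sectional outcomes as in-hospital maternal death and near-miss discharged alive. Count readmissions to participating hospitals within 42 days, and state how a readmission is linked to the index record given that chart data do not identify the woman.
- Report transferred women as a separate category with outcome unknown. Add a sensitivity analysis that counts them all as survivors and then all as deaths.
- Describe the odds ratios as associations with death in participating hospitals.
- Do not use the 3-month call to bound the misclassification.

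The cost is mainly rewording, a linkage rule and one added sensitivity analysis. The downside is that the headline figures become in-hospital rather than 42-day figures.

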#### Maternal potentially life threatening condition

A condition of severe morbidity found in women during pregnancy, childbirth or in the puerperium, classified as potentially life threatening conditions [5], including hemorrhagic or hypertensive disorders, other systemic disorders, and indicators of severe management (Appendix 2).

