#### Conditions at birth

Vital status of the newborn infant as recorded on the medical chart, dichotomized into live or intrauterine death.

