### Data analysis

Data analysis will be performed in sub-groups according to the time of occurrence of the near-miss or severe maternal morbidity (in adolescence, older ages or at another time in the woman's reproductive life) and determining cause (hypertension, hemorrhage, abortion or other causes). The rates of maternal near-miss will be calculated for each collaborating center using the WHO maternal near miss approach [5], and frequencies of non-near-miss severe maternal morbidity will be calculated using specific defined diagnoses. General estimates will be calculated together with their respective 95% confidence intervals. The association between organ dysfunction and maternal death will be estimated using odds ratios, likelihood ratio test and their respective 95% confidence intervals. In addition, relative risks will be calculated for sexual dysfunction, postpartum depression, posttraumatic stress disorder, deterioration in quality of life, deterioration in the woman's perception of her own functional status in routine activities, risk of adverse perinatal outcome and risk of impaired neuromotor and weight-height development in the children born from the pregnancy associated with severe maternal morbidity.

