### Management Criteria

Use of continuous vasoactive drug

Dialysis for treatment of acute kidney failure

Puerperal hysterectomy due to infection or hemorrhage

Cardiopulmonary resuscitation (CPR)

Transfusion ≥ 5 units of red blood cell concentrate

Intubation and ventilation for a period ≥ 60 minutes, unrelated to anesthesia*

Modified from [5]

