## Appendix 2: Indicators of non-near-miss severe maternal morbidity (potentially life-threatening conditions) *

### Hemorrhagic disorders

Abruptio placentae

Placenta accreta/increta/percreta

Ectopic pregnancy

Antepartum hemorrhage

Postpartum hemorrhage

Ruptured uterus

Abortion with severe hemorrhage

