### Other systemic disorders

Endometritis

Pulmonary edema

Respiratory failure

Seizures

Sepsis

Thrombocytopenia <100,000

Thyroid crisis

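### For vital status at birth and Apgar, the planned perinatal relative risk includes women whose first severe complication began after the birth, so for them the outcome comes before the exposure

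*Protocol article*

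**What the plan says.** All references are to the protocol article.

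- **Exposure.** Methods/Design states for the cohort: "The main exposure factor will be the occurrence of severe maternal morbidity". It adds that both potentially life-threatening and near-miss conditions count.
- **Exposure window.** Under Main outcomes, a potentially life-threatening condition is "A condition of severe morbidity found in women during pregnancy, childbirth or in the puerperium". The near-miss definition runs to 42 days postpartum.
- **Qualifying items.** Appendix 2 lists "Postpartum hemorrhage", "Endometritis" and a hospital stay of more than 7 postpartum days. Appendix 1 lists "Puerperal hysterectomy due to infection or hemorrhage".
- **Outcomes.** Conditions at birth is vital status, "dichotomized into live or intrauterine death". Vitality of the newborn is the Apgar score at 1 and 5 minutes. Neonatal outcome covers deaths up to 28 days.
- **Analysis.** Data analysis plans relative risks that include the "risk of adverse perinatal outcome". It also plans subgroups by time of occurrence, which it defines by the woman's age or reproductive stage, and by determining cause.
- **Hypothesis and aim.** Main hypotheses expects a poorer immediate perinatal outcome in these pregnancies. Methods/Design gives the cohort's purpose as the repercussions of severe morbidity.

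**The concern.** The broad window suits the first aim, which is to count severe morbidity up to 42 days after pregnancy. The cohort reuses it unchanged as the exposure for outcomes that are fixed at the birth or within five minutes of it. A hemorrhage or uterine infection that starts later cannot have caused an intrauterine death or a low Apgar score. The direction may even be reversed or shared, since a fetal death or a difficult birth can be followed by bleeding, infection or a return to the operating room.

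At stake is the reading of one directional hypothesis. If exposed women have more stillbirths or lower Apgar scores, a single relative risk does not show whether this reflects morbidity that preceded the birth or births that preceded the morbidity. If the estimate is small, it does not show whether an effect of earlier morbidity has been diluted.

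**Working it through.** **Plan's own figures.** The only sample-size figures are for the cross-sectional part: 75,000 × 8/1000 = 600 near misses, as stated, and 75,000 × 140/100,000 = 105 deaths, against about 100 stated. They do not bear on this point. The article gives no share of women by onset and no perinatal risk.

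**Step 1: time order, from the article's own definitions.**

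| Start of first complication | Vital status at birth, Apgar | Neonatal death to 28 days | Infant development at 6 months |
|---|---|---|---|
| Before or during birth | exposure can come first | exposure comes first | exposure comes first |
| After birth | outcome comes first | either order possible | exposure comes first |

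The time-order fault is certain only for after-birth onset with the two birth outcomes.

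**Step 2: do the stated subgroups separate the onset groups?** Time of occurrence means maternal age or reproductive stage, so it does not. The cause groups are hypertension, hemorrhage, abortion and other. Appendix 2 places placental abruption, antepartum hemorrhage and postpartum hemorrhage together among the hemorrhagic disorders, so the hemorrhage group mixes the two onsets.

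**Step 3: effect on the estimate.** Let f be the share of exposed women with onset after birth, RR_b and RR_a the relative risks against the same controls for onset before or during birth and after it, and p0 the control risk.

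Risk in the exposed = (1 − f) × RR_b × p0 + f × RR_a × p0. Dividing by p0:

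Pooled RR = (1 − f) × RR_b + f × RR_a.

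All values below are assumed, for illustration only.

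| f | RR_b = 2.0, RR_a = 1.0 | RR_b = 1.0, RR_a = 2.0 |
|---|---|---|
| 0.1 | 0.9 × 2.0 + 0.1 × 1.0 = 1.90 | 0.9 × 1.0 + 0.1 × 2.0 = 1.10 |
| 0.2 | 1.80 | 1.20 |
| 0.3 | 1.70 | 1.30 |
| 0.5 | 1.50 | 1.50 |

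The first column is a real effect that is diluted. The second is no effect of earlier morbidity, with an excess that comes only from wrongly ordered pairs. At f = 0.5 both give 1.50, so the pooled figure alone cannot tell them apart.

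**The case against.** There are four serious points on the other side.

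1. *The child objective and hypotheses claim less than causation.* They speak of pregnancies associated with severe morbidity, and a comparison of such pregnancies with others needs no ordering of onset. This stands in part. The softer wording is real, but Methods/Design calls morbidity the exposure and repercussions the purpose, and the hypothesis is directional. A relative risk against unexposed controls will be read in that light.

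2. *An onset split may sit in the full protocol, analysis plan or case form, which are not shown.* It may, and the article does describe recording the first complication in the chain and the hospital days before and after delivery. But the article states the exposure, the outcomes and the subgroups. It uses the words for a time-of-occurrence split with another meaning. As stated, the plan puts the wrongly ordered pairs into the analysis.

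3. *The size is unknown.* This stands in full. The table in the working is a weighted average of assumed values.

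4. *Splitting by onset may not be enough for stillbirth.* Methods/Design draws controls from rooming-in wards, which may under-represent women with a stillborn infant, whereas the Longitudinal component makes all same-day obstetric admissions without severe conditions eligible. This is a separate question that an onset split does not settle.

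A reader might also infer that the perinatal relative risk is worthless, or that the fault extends to all child outcomes. The documents support neither. Conditions such as abruption or antepartum hemorrhage precede the birth, and neonatal death to 28 days and six-month development can follow puerperal morbidity.

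**Conclusion.** The point holds for two outcomes, vital status at birth and Apgar, and for one group, women whose first severe complication began after the birth. For them the outcome precedes the exposure under the article's own definitions, and no stated subgroup separates them. The pooled relative risk lies between the two onset-specific values: it is diluted where the after-birth value is the lower and inflated where it is the higher. Neither the direction nor the amount can be determined from the documents.

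This rests on two premises: that the perinatal relative risk uses the cohort's exposure as defined, and that some exposed women have after-birth onset, which the listed conditions make hard to doubt. The hypotheses on quality of life, posttraumatic stress, depression, sexual function and functional status are unaffected, as is six-month infant development as far as time order goes.

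**What to change.** - Classify each exposed woman's onset as before or during birth, or after birth. Use the start of the first complication in the chain, which is already recorded, and not the date on which an indicator was met. A long postpartum stay or a hysterectomy may stem from a condition that began earlier.
- Where the name of the condition does not reveal its timing (sepsis or eclampsia, for example), the form needs an onset item if it does not already have one.
- Base the relative risks for stillbirth and Apgar on women with onset before or during birth. Report women with later onset separately and describe that result as an association only.
- For neonatal death to 28 days and six-month infant development, keep all exposed women and show the results by onset.
- State in Data analysis that this split is distinct from the subgroups by maternal age.

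The cost is at most one form item and a few sentences of analysis text. The downside is a smaller exposed group, and so a wider confidence interval, for the two birth outcomes.
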